**5. Association between quality of life (QoL), lifestyle and amyloid deposition (PI: [name])**

We hypothesize that higher score in QoL questionnaires will be associated with less amyloid deposition. The objectives of this exploratory analysis are to know (a) what is the QoL subscore that best predict amyloid deposition ? (b) is QoL related to other psychoaffective measurements? and finally, (c) are the effects of QoL on amyloid deposition independent of psychoaffective factors?

To answer to those questions, statistical analyses will be conducted on the data of LoQ questionnaires and florbetapir-PET.

Firstly, we will identify those lifestyle and psychoaffective factors that are associated to QoL as confounders, by using univariate analyses, from the following list and include the significant ones as covariates: Lifestyle (Modifiable Activities Questionnaire (MAQ) or Physical activity for the Elderly (PASE), Mediterranean Adherence Screener (MEDAS), Alcohol consumption, Self-medication, Smoking); Cognitive Complaints, Depression (GDS), anxiety (STAI).

Then, a multivariate analysis by using a multiple regression analysis (voxel-wise) between QoL scores and florbetapir PET (controlling for age and sex) will be performed.

Finally, in following models we will control for potential confounding variables (i.e., those that are significantly related to QoL) in order to test for independent effects.

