**12. Biological determinants of ageing and risk factors of AD (PI: [name])**

For these exploratory analyses, all blood biomarkers will be analysed and then a) regression analyses and b) group comparisons will be conducted to assess the effects of age on blood biomarkers, the links between the blood biomarkers and the other markers of mental health and well being, as well as how populations (defined according to their risk of AD) differ in terms of blood biomarkers.

**13. Relationships between lifestyle and subjective and objective sleep quality (PI: [name] & [name])**

We hypothesize that lifestyle with little stress; stimulating social, physical and cognitive activities will be associated with better sleep quality.

For this purpose, sleep parameters and lifestyle variables will be analysed.

After that, group comparisons, multivariate analysis by using multiple regression analysis will be used after adjusting for covariates having a significant effect in the sample of participants or well-described in the literature.

**14. Relationships between objective and subjective sleep quality and blood-based markers of ageing and AD (PI: [name] & [name])**

We hypothesize that poor sleep quality or objective sleep disturbances will be related to changes of some blood-based markers sensitive to stress, ageing and AD.

Several parameters including: sleep parameters, ageing, AD, stress, mood, inflammation blood markers, will be exploited and group comparisons, multivariate analysis by using multiple regression analysis will be used after adjusting for covariates having a significant effect in the sample of participants or well-described in the literature.

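### Objective 6 item 5 tests whether the quality-of-life and amyloid association is independent of psychoaffective factors after dropping every listed factor that is not significantly related to quality of life

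*Combined protocol and SAP*

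**What the plan says.** Item 5 under Objective 6 of the SAP for secondary objectives relates QoL to florbetapir-PET amyloid in non-expert seniors at baseline. It labels itself exploratory ("The objectives of this exploratory analysis are to know") and poses three questions: (a) which QoL subscore best predicts amyloid, (b) whether QoL is related to other psychoaffective measures, and (c) whether any effect of QoL on amyloid is independent of psychoaffective factors.

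The steps are:

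1. Screen a fixed list: "we will identify those lifestyle and psychoaffective factors that are associated to QoL as confounders, by using univariate analyses", then "include the significant ones as covariates". The list holds physical activity (MAQ or PASE), Mediterranean diet, and "Alcohol consumption, Self-medication, Smoking); Cognitive Complaints, Depression (GDS), anxiety (STAI"). That is eight factors if MAQ or PASE counts as one.
2. Fit a voxel-wise multiple regression of amyloid on QoL, "controlling for age and sex".
3. In later models, "we will control for potential confounding variables (i.e., those that are significantly related to QoL) in order to test for independent effects".

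Item 5 sets no significance level for the screen. The Type I error rate section of the same SAP gives two-sided 5% for each of the other secondary tests. Neighbouring items work differently: item 4 names MMSE, GDS and IRI as adjustment variables and item 6 names STAI, GDS, age and sex, with no screen in either.

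**The concern.** Question (c) is about independence from psychoaffective factors, but which of them are adjusted for is decided by a significance test in the same data. Three problems follow.

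- A non-significant univariate test does not show that a factor is unrelated to QoL. With about 135 people, modest correlations often fail to reach 5%.
- Confounding depends on the product of two links, factor with QoL and factor with amyloid. The screen looks only at the first, so a factor strongly related to amyloid and modestly related to QoL can be dropped.
- Depression (GDS) or anxiety (STAI) could fail the screen. Question (c) would then be answered without adjusting for the very factors it names.

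Several weak confounders, each dropped, could jointly produce a QoL and amyloid association that is then described as independent.

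**Working it through.** **Inputs.** Non-expert seniors included: 135 (Lockdown substudy annex, Participants). Planned: 150, or 126 before the addition (sample size sections). Candidate factors: eight (item 5). Screen: two-sided 5%. The plan gives no power or miss rate for the screen, so there is no stated figure to reproduce. All correlations below are assumptions.

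**How often a real factor is dropped.** By Fisher's z, with true correlation r between factor and QoL:

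miss rate = 1 − [Φ(atanh(r)·√(n−3) − 1.96) + Φ(−atanh(r)·√(n−3) − 1.96)]

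- n=135, r=0.20: 0.2027 × √132 = 0.2027 × 11.489 = 2.329; Φ(0.369) = 0.644; miss rate 35.6%.
- n=135, r=0.15: 0.1511 × 11.489 = 1.736; Φ(−0.224) = 0.411; miss rate 58.8%.

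| n | r=0.10 | 0.15 | 0.20 | 0.25 | 0.30 | 0.40 |
|---|---|---|---|---|---|---|
| 126 | 80% | 61% | 39% | 19% | 7.0% | 0.3% |
| 135 | 79% | 59% | 36% | 16.5% | 5.5% | 0.2% |
| 150 | 77% | 55% | 31% | 13% | 3.7% | 0.1% |
| 250 (assumed, if cohorts are pooled) | 65% | 34% | 11% | 2.0% | 0.2% | 0.0% |

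**What one dropped factor costs.** If a factor correlated 0.15 with QoL and with standardised effect 0.20 on amyloid is always omitted, the bias in the standardised QoL coefficient is 0.15 × 0.20 = 0.03. The standard error of that coefficient is about 1/√133 = 0.087, so the bias is about a third of a standard error. Under the screen the mean bias is smaller, about 0.011, because the factor is omitted mainly in samples where its observed correlation with QoL is low. With eight such independent factors the mean bias under the screen is about 0.10, a little over one standard error.

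**False-positive rate for the QoL coefficient.** Simulation with n=135, 6,000 replicates, a single amyloid value as outcome, no true QoL effect, and nominal 5%. The columns after the first two give each factor's correlation with QoL and with amyloid, then the rejection rates.

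| Factors | Structure | QoL / amyloid | Screened | All listed factors in |
|---|---|---|---|---|
| 1 | – | 0.15 / 0.20 | 5.2% | 5.0% |
| 3 | independent | 0.15 / 0.20 | 6.5% | 5.1% |
| 8 | independent, same direction | 0.15 / 0.15 | 13.8% | 5.2% |
| 8 | independent, same direction | 0.15 / 0.20 | 22.4% | 5.3% |
| 8 | independent, same direction | 0.20 / 0.20 | 19.2% | 5.3% |
| 8 | independent, random directions | 0.15 / 0.20 | 7.1% | 4.6% |
| 8 | intercorrelated 0.1 | 0.15 / 0.20 | 6.1% | 5.0% |
| 8 | intercorrelated 0.3 | 0.15 / 0.20 | 4.6% | 5.0% |

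In the intercorrelated rows the marginal correlations are held fixed. Each factor's separate contribution is then smaller, and the retained factors stand in for the dropped ones.

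**Feasibility of full adjustment.** Intercept, QoL, age, sex and eight factors use 12 parameters, so 135 − 12 = 123 residual degrees of freedom remain.

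**The case against.** The strongest case on the other side has several parts.

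- **Only weak factors are lost.** A factor correlated 0.30 or more with QoL is dropped at most 5.5% of the time at n=135. The SAP also allows pooling with SCD-Well and IMAP+ when relevant, which would cut the miss rate further. This stands, and it is why no single miss rate describes the screen.
- **The inflation needs an unfavourable structure.** Depression, anxiety and cognitive complaints are unlikely to be mutually independent, and a correlation of only 0.1 among the factors removes most of the excess. This stands. The 14-22% is the bad end of a range, not an expected rate.
- **The analysis is voxel-wise.** The simulated rates are for one amyloid value and do not carry over to a voxel map. This stands as a limit on the numbers, not on the logic of the screen.
- **The screen has a purpose of its own.** It answers question (b). True, and it can stay for that, but answering (b) does not require (c) to depend on it.
- **Full adjustment is not automatically safer.** Cognitive complaints, GDS and STAI might lie downstream of amyloid or overlap with QoL. That limits any causal reading. But (c) asks specifically about independence from psychoaffective factors, so they must be in the model that answers it.
- **Other sections provide for adjustment.** Protocol 11.3.6 commits secondary analyses to confounder adjustment, and the SAP's imaging section allows further covariates as required. Neither overrides the specific rule in item 5.

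A reader might also infer that the plan asserts independence. It does not; it asks the question in an exploratory analysis. Nor do Objective 7 items 13 and 14 repeat the defect: they adjust "after adjusting for covariates having a significant effect in the sample of participants or well-described in the literature", so a covariate supported by the literature stays in whatever its p-value.

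**Conclusion.** The point holds as a minor one. As written, item 5 cannot support a statement that the QoL and amyloid association is independent of psychoaffective factors, because a listed factor leaves the model whenever its univariate test against QoL is not significant, whatever its relation to amyloid.

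The size is uncertain. At n=135 a factor correlated 0.15 to 0.20 with QoL is dropped 59% to 36% of the time, but that band is an assumption and the rate runs from 79% at 0.10 to 0.2% at 0.40. The false-positive rate is close to nominal with one to three weak factors or with modest intercorrelation, and reaches about 14-22% only with eight independent factors acting in the same direction at 0.15 with QoL and 0.15 to 0.20 with amyloid. The trial's primary objectives are not affected.

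**What to change.** In Objective 6 item 5:

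- Keep the univariate analyses, but only as the descriptive answer to question (b).
- Base question (c) on one prespecified model with age, sex and all eight listed factors, and fix in advance whether MAQ or PASE is used. This follows what items 4 and 6 already do for their covariates.
- Fit it voxel-wise as planned. If a coefficient and 95% confidence interval are wanted, fit the same model to the global cortical amyloid value that protocol section 10.6.2 already derives; a voxel map does not yield a single coefficient.

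The cost is SAP wording, about eight degrees of freedom (123 left at n=135, fewer if questionnaire data are incomplete) and a slightly wider interval, more so if the psychoaffective scales overlap strongly with QoL. No change to Objective 7 items 13 and 14 is needed on this ground.

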**6. Identify lifestyle predictors of memory complaints and their clinical significance (PI: [name])**

We hypothesize that work, social environment, lifestyle and personal attitudes and beliefs will be associated to subjective cognitive complaints and modulate the relationship between complaints and (a) cognition and (b) AD biomarkers. The objectives of this analysis are to know (a) what are the best lifestyle predictors of cognitive complaints; (b) How do those factors modulate the relation between cognitive complaints and cognition or AD biomarkers?

The statistical analysis will be conducted on two steps with available data including: lifestyle and QoL questionnaires, cognitive complaints questionnaire, AD biomarkers (whole brain structural MRI, FDG and AV45), cognition (z-scores).

- STEP 1: Multiple regression analysis between cognitive complaints and lifestyle factors (probably lifestyle measurements will be reduced in "dimensions" or "factors" using factors analyses)
- STEP 2: (a) Multivariate analyses between the factors identified in STEP1 and cognition (including anxiety (STAI), depression (GDS), age and sex as covariates). Then, we will test for main effects and interactions (i.e., how the identified factors modulate the relation between cognitive complaints and cognition) (b): Multivariate analyses between factors identified in STEP1 and AD and aging biomarkers (including anxiety (STAI), depression (GDS), age and sex as covariates). Then, we will test for main effects and interactions.

## **7. Lifestyle by APOE interactions on vascular risk, hippocampal volume and amyloid deposition (PI: [name])**

We hypothesize that APOE status will have differential as well as dose-dependent effects on vascular risk, hippocampal volume and amyloid deposition.

Accordingly, the primary aims of this analysis were to investigate: (a) what are the protective/risk effects of APOE polymorphism on vascular risk factors, hippocampal volume and amyloid deposition; (b) is there a dose-dependent effect of APOE4? (c) How do these protective or risk effects interact with lifestyle?

Thus, lifestyle questionnaires, cognition (z-scores), florbetapir-PET, FDG-PET, MRI, vascular risk factors (cholesterol levels, diabetes, BMI) will be exploited. A multivariate analyses will be conducted (sex and age as covariates) including APOE4 status (e2, e4, e4e4), lifestyle (factors reduced in dimensions) and vascular risk (as dependent variable-model 1); or hippocampal volume (as dependent variable-model 2) or florbetapir-PET (as dependent variable-model 3). Finally, we will test for main effects and interactions. If more than one model is significant, we will perform another model including the significant variables.

## **8. Does lifestyle underlie the gender bias in AD? (PI: [name])**

We hypothesize that there will be gender specificities in lifestyle variables that will be differentially associated to brain measurements. For this purpose, lifestyle questionnaires, vascular risk, florbetapir-PET, structural MRI, FDG-PET, APOE genotype, cognition (z-scores) will be exploited and several comparisons will be then performed:

- (1) Between groups comparison in lifestyle habits (t-test, women vs men).
- (2) Between groups comparison in AD biomarkers and cognition.
- (3) Mediation and moderation analyses of lifestyle factors on the biomarkers or cognitive domains where there are gender differences.
- (4) Sub-analyses in women.

## **9. Identify the combination of lifestyle risk and protective factors that are associated with the cognition vs AD biomarkers across disease stages (PI: [name])**

This exploratory analysis aims to evaluate the combination of lifestyle risk and protective factors that are associated with the cognition versus AD biomarkers across disease stages. For that, lifestyle questionnaires, AD and aging biomarkers (whole brain structural MRI, FDG and AV45) as well as clinical status of participants, will appropriately be exploited. A multiple regression analyses between lifestyle factors and AD and aging biomarkers including clinical group will be conducted. Finally, we will test for main effects and interaction by group.

## **10. Relationship between lifestyle and blood markers? (PI: [name])**

This exploratory analysis aims essentially to determine the relationship between lifestyle and blood markers. General health biomarkers and lifestyle variables will be exploited and regression analysis and group comparisons will be then performed

## **Objective 7 (WP 1 to 6)**

All biomarkers variables and gender of both populations (experts in meditation and senior non-experts, separately) will be used to find a link between the biomarkers of Alzheimer disease (AD) and structural and/or functional connectivity on the spread of lesions. All analyses will be conducted on the participants of Age-Well study at baseline visit.

### **1. Relationships between age and AD risk factors on the one hand and attention measured with the Flanker task on the other hand (PI: [name])**

We hypothesize that age and AD risk factors will be associated with lower attention performances in specific attention subscore.

The Flanker task (orienting, executive function, alerting measures), T1 volume of grey matter density and PET measures of FDG and amyloid measures, alzheimer risk factors, memory complaints and family background, will be used.

Group comparisons and regressions analyses will be done after adjusting for age, gender, education and years of retreat.

### **2. Relationship between sleep quality and attention (PI: [name])**

We hypothesize that low sleep quality will be associated with decreased attentional performances.

For this purpose, orienting, executive function, possibly other behavioural measures of attention, measures of sleep quality including questionnaires, actimetry and polysomnography index will be used and group comparisons and/or regressions will be conducted after adjusting for age, gender, education and years of retreat.

### **3. Links between AD-risk factors and attention performances and neural substrates (PI: [name])**

We hypothesize that AD risk factors will be associated with decreased attention performances related with changes in brain activations (both increase and decrease activations).

For this purpose, attentional and executive measures from the neuropsychological battery as well as whole-brain analyses of fMRI data acquired during the attentional task will be exploited and analyses between groups (after adjusting for sex and age) will be performed with or without AD risk factors.

### **4. Relationship between emotion and personality traits on attentional efficiency (PI: [name] + [name])**

We hypothesize that higher attentional efficiency is associated to some emotion and personality traits.

The objective of this analysis is to show if there is, or not, a link between brain emotional reactivity and cognitive performances.

For this purpose, functional MRI and behavioural scores will be exploited and a regression analysis, after adjusting for sex, age, cognitive emotional scores post-MRI will be used.

### **5. Validation of SoVT-REST in elderly/ Relationships between emotional fMRI data and resting state fMRI data & Neural response to emotional task during and after stimulation (fMRI, Baseline) (PI: [name])**

The main objectives of this analysis are to evaluate i) differences between exposure to emotional vs. non emotional videos and emotional inertia levels; ii) Effects of connectivity patterns in Default Mode Network during resting state on brain reactivity during and after emotional exposure, iii) Relationship between Emotion probes and brain activity in SoVT-Rest.

For this purpose, fMRI, post-SoVT, and some questionnaires. Repeated measures MANOVA, T-tests, post hoc corrections (i.e. Bonferroni); Functional whole brain connectivity/ group comparisons; Regression analysis/ ROI analysis / data-driven lexico-semantic mapping will be used.

### **6. Identify the relationships between age/AD risk factors and emotions (PI: [name])**

We hypothesize that age and AD risk factors will be associated with changes in emotion measures.

The main objective of this analysis is to determine the effects of AD biomarkers on emotional processing.

For this purpose, functional MRI during emotional task, ageing/AD biomarkers; memory complaints; family background; structural MRI, FDG-PET and AV-45 PET whole brain will be exploited. Correlation analysis and group comparisons will be conducted after adjustment for cognitive and emotional scores (MMSE, GDS, IRI).

### **7. Impacts of traits on caregiving, loneliness and prosociality in elderly (PI : [name])**

We hypothesize that there will be significant relationships between specific traits and caregiving and/or prosociality.

For these purposes, all parameters related to mindfulness, compassion, emotions and caregiving will be exploited and then hierarchical linear model with sex (level 1), group (level 2) and outcome variables will be performed. If necessary, correlations, covariations and cluster analyses may be also used.

### **8. Relationships between emotions, emotional fMRI data and sleep/stress/ lifestyle and serotonin levels (PI: [name]).**

We hypothesize that quality of sleep and level of stress will be related with behavioural measures of emotions and fMRI measures of the neural substrates of emotion.

Several parameters including : sleep measures, emotion measures, blood measure of stress, emotion questionnaires, SoVT Rest, and lifestyle quality measures will be exploited and hierarchical linear model with sex (level 1), group (level 2) and outcome variables will be used. If necessary, correlations, covariations and cluster analyses may also be used.

### **9. Cognitive debt and relation to dementia risk (biological markers) (PI: [name]).**

We hypothesize that higher cognitive debt will be associated with higher dementia risk.

For this purpose, several parameters will be exploited including: depression, anxiety, neuroticism, rumination, worry, biomarkers, ((Alzheimer risk factors: APOE4, AMYLOID Abeta+/- (0.1 and linear); Memory complaints; Family background; structural MRI, FDG-PET and AV-45 PET whole brain), and cognition.

A multivariate analysis by using factor method will be used and regression analysis will be conducted to evaluate the relationship between these late factors.

**10. How is cognitive debt related to latent mindfulness / meditation factor? (PI: [name]).**

For this exploratory analysis, several parameters will be exploited including: depression, anxiety, neuroticism, rumination, worry, biomarkers, ((Alzheimer risk factors: APOE4, AMYLOID Abeta+/- (0.1 and linear); Memory complaints; Family background; structural MRI, FDG-PET and AV-45 PET whole brain), and cognition.

A multivariate analysis by using factor method will be performed and regression analysis will be conducted to evaluate the relationship between these late factors.

**11. Relationships between cognitive debt and cognition and between cognition and mindfulness (PI: [name]).**

For this exploratory analysis, several parameters will be exploited including: depression, anxiety, neuroticism, rumination, worry, biomarkers, and cognition.

A multivariate analysis by using factor method will be used and regression analysis will be made to evaluate the relationship between these late factors.

**12. Biological determinants of ageing and risk factors of AD (PI: [name])**

For these exploratory analyses, all blood biomarkers will be analysed and then a) regression analyses and b) group comparisons will be conducted to assess the effects of age on blood biomarkers, the links between the blood biomarkers and the other markers of mental health and well being, as well as how populations (defined according to their risk of AD) differ in terms of blood biomarkers.

**13. Relationships between lifestyle and subjective and objective sleep quality (PI: [name] & [name])**

We hypothesize that lifestyle with little stress; stimulating social, physical and cognitive activities will be associated with better sleep quality.

For this purpose, sleep parameters and lifestyle variables will be analysed.

After that, group comparisons, multivariate analysis by using multiple regression analysis will be used after adjusting for covariates having a significant effect in the sample of participants or well-described in the literature.

**14. Relationships between objective and subjective sleep quality and blood-based markers of ageing and AD (PI: [name] & [name])**

We hypothesize that poor sleep quality or objective sleep disturbances will be related to changes of some blood-based markers sensitive to stress, ageing and AD.

Several parameters including: sleep parameters, ageing, AD, stress, mood, inflammation blood markers, will be exploited and group comparisons, multivariate analysis by using multiple regression analysis will be used after adjusting for covariates having a significant effect in the sample of participants or well-described in the literature.

